### Data to be collected during the procedure

- Guidewire activation to guidewire retraction
- Fluoroscopy time
- Participant and staff radiation exposure (dose area product (DAP) and air kerma (AK))
- Lesion characteristics (eg tortuosity, calcification and bifurcation)
- Operator assessment of stent length
- Robotic assessment of stent length
- Contrast volume
- Procedure end time (Guide Catheter out)
- Equipment utilisation
- Pre and post PCI stenosis percentage
- Need for manual input (if required) and reason for this
- Number of times stent visualisation technique (eg stent boost or clearstent) used
- Use of robotic algorithms (techIQ) to assist lesion navigation
- Any adverse events
- Use of intracoronary physiology and/or intracoronary imaging
- Operator survey of task load

### Standard PCI Technique

PCI will be performed as per the Institutional PCI procedure. Operators will be encouraged to raise the operating table as high as possible and use shuttering and collimation techniques to limit X ray exposures to the patient and staff.

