### Participant and Staff Radiation Exposure

DAP (dose-area-product) and cumulative dose/air kerma, as recorded during the PCI procedure. Radiation exposure to the patient and staff will be measured by personal dosimeters (Polimaster PM1610) placed at the left shoulder.

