## **Randomisation**

Participants will be randomized 1:1 to the PCI performed using standard care or technology-assisted PCI in blocks to ensure balanced distribution of the treatment groups at all times. The study team will enter the participant screening information into the electronic data capture (EDC) system after informed consent has been obtained. Once the participant is determined to be eligible prior to the Index Procedure the study team will randomise the participant using the EDC. The Investigator will be advised of this and the allocated method of PCI will be performed. The participant will ideally remain blinded to the method of PCI performed.

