### CorPath Use Technique

The operator should refer to the CorPath GRX System Operator’s Manual for a detailed description of the system and relevant techniques.

To obtain proper data for analysis, the following procedure, with associated data collection milestones, is recommended, but in no case, dictates use of the CorPath GRX System in a manner different from that presented in the Operator’s Manual:

1. Obtain access using conventional percutaneous catheterization techniques.
2. Once arterial access is obtained, insert a standard guide catheter using conventional techniques. The guide catheter and guidewire of the physician’s choosing shall be used.
3. Manually advance and engage the guide catheter in the coronary artery. Perform angiography to assess the target lesion(s). Record target lesion characteristics such as percent diameter stenosis, etc.
4. Introduce and advance coronary guidewire utilizing CorPath GRX System to target lesion.
5. Record visual estimate of lesion segment (prior to pre-dilatation).
6. Introduce and advance the therapeutic coronary device (balloon/stent) using the CorPath GRX System. The delivery of interventional dilatation and stenting devices to the target lesion (pre-dilation, stent, post dilatation) will be done using the CorPath GRX System. Active guide management may be used to fine tune the placement of or reengage the guide catheter in the ostium of the coronary artery.
7. Measure target lesion using the CorPath GRX System as described in Section 3.5.
8. After stent placement, measure stent length using the CorPath GRX System as described in Section 3.5.
9. Retract balloon/stent system using CorPath GRX System.
10. Retract the guidewire using the CorPath GRX System.
11. Perform completion angiography to assess the target lesion final diameter stenosis and the condition of associated vasculature.
12. Record final fluoroscopy time.
13. Record time of guide catheter removal from the coronary vessel (procedure end time).

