# Data Management, Statistical Analysis and Record Keeping

## **Statistical Methods**

This is a double-arm, open-label, randomized controlled trial of the CorPath GRX System designed to evaluate the safety and effectiveness of the clinical and technical performance of the CorPath GRX System in the delivery and manipulation of coronary guidewires and stent/balloon catheters, and remote manipulation of guide catheters for use in PCI in comparison to standard of care. The analysis of data collected as part of the RCT will include, but may not be limited to, the Objectives and Measures outlined in Section 3.0 of this protocol. Continuous variables will be summarized using the number of observations, mean, standard deviation, median, min and max values. Categorical variables will be summarized with the number and percent in each category out of the number observed. Two-sided 95% confidence intervals may be calculated and two-sided p-values < 0.05 will be considered statistically significant.

The outcome of patient radiation exposure will be analysed using variance (ANOVA). As each participant may have multiple lesions, the outcome of clinical success at day 3 will be analysed using a two level multilevel models. Logit link will be used with a binomial distribution and restricted maximum likelihood (REML) will be used for estimation. Predictor variables in the models will include treatment group.

Technical success will analysed with Fisher’s exact test, comparing the proportion of participants with technical success between the two groups. Logistic regression will be used to compare technical success accounting for lesion complexity. For all other secondary outcomes, continuous outcomes will be measured using independent t-test (or non-parametric alternative depending on distributional assumptions), and categorical outcomes analysed by Fisher’s exact test. For outcomes measured repeatedly over time, multilevel models with an appropriate link functions will be used for analysis.

All statistical analyses will be performed using SAS software (version 9.4) or other widely accepted statistical or graphical software.

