A total sample of 300 patients (150 in each group) is sufficient to detect a 20% reduction in radiation exposure to the patient during PCI, assuming a mean radiation exposure of 1284 mGy with standard deviation 180 mGy in the control group, and a standard deviation of 142.83 in the intervention group (29) with greater than 99% statistical power, and two sided statistical significance of 5%.

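### Dose-limiting steps are encouraged only in the standard PCI arm, so open-label operators could apply them unequally on the patient-dose outcome that sizes the trial

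*Protocol*

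**What the plan says.** Section 7.2.4 (Standard PCI Technique) refers operators to the institutional PCI procedure and then adds: "Operators will be encouraged to raise the operating table as high as possible and use shuttering and collimation techniques to limit X ray exposures". Its stated purpose covers patients as well as staff: "to limit X ray exposures to the patient and staff".

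Section 7.2.5 (CorPath Use Technique) sends the operator to the CorPath Operator's Manual "for a detailed description of the system and relevant techniques" and lists 13 recommended steps. None concerns table height, shuttering, collimation or any other way of limiting dose. The only X-ray item is the recording of fluoroscopy time.

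Section 5.3 has the operator informed of the randomised arm before the procedure: "The Investigator will be advised of this and the allocated method of PCI will be performed". Section 8.1 confirms that the trial is not blinded at operator level: "This is a double-arm, open-label, randomized controlled trial of the CorPath GRX System".

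Patient dose is captured as "DAP (dose-area-product) and cumulative dose/air kerma, as recorded during the PCI procedure" (section 2.6.5). It is the only outcome in the sample-size statement in section 8.1, where a total of 300 "is sufficient to detect a 20% reduction in radiation exposure to the patient during PCI". Section 8.1 plans an ANOVA for it.

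**The concern.** The Protocol writes a dose-limiting co-intervention into one arm of a dose comparison, and the people who can apply it know which arm they are in. If uptake differs, the difference arises after randomisation, so randomisation does not protect against it. The planned ANOVA cannot separate the effect of the device from the effect of table height and beam collimation.

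Higher uptake in the standard arm would lower the control dose and shrink an apparent robotic benefit. It would not create a false benefit. What is at stake is mainly the estimate: readers will want to know how large the reduction is, and a shrunken figure is still wrong. If the device has no effect on patient dose, unequal practice could make it appear to increase dose.

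There is also a plain safety reason for equal advice. Patients and bedside staff in the CorPath arm should have the same encouragement as those in the standard arm.

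**Working it through.** **Inputs from the Protocol (section 8.1).** 150 per arm; control mean 1284 mGy, SD 180; intervention SD 142.83; reduction to detect 20%; two-sided 5%; stated power above 99%.

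**Inputs that are assumed, because the Protocol gives none.** The proportional dose cut from the steps where they are used, *e* = 5, 10 or 15%; and uptake in the control arm *uC* and the CorPath arm *uR*. The stated SDs are held fixed.

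**Step 1: reproduce the stated power.** Difference = 0.20 × 1284 = 256.8 mGy. SE = √(180²/150 + 142.83²/150) = 18.76 mGy, with Welch df 283. Difference/SE = 13.7, so power is essentially 1, which agrees with the Protocol.

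**Step 2: how small a difference is significant.** 1.96 × 18.76 ≈ 36.8 mGy, which is 36.8/1284 = 2.9% of the control mean. On the stated SDs, the trial would pick up small systematic differences in practice.

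**Step 3: observed reduction when the true device effect is 20%.**

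Observed reduction = 1 − 0.80 × (1 − *e*·*uR*)/(1 − *e*·*uC*)

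| Uptake, control vs CorPath | *e* = 5% | *e* = 10% | *e* = 15% |
|---|---|---|---|
| 100% vs 0% (extreme) | 15.8% | 11.1% | 5.9% |
| 100% vs 50% | 17.9% | 15.6% | 12.9% |
| 100% vs 75% | 18.9% | 17.8% | 16.5% |
| Equal | 20.0% | 20.0% | 20.0% |

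For example, with *e* = 10% and 100% vs 0%: 1 − 0.80/0.90 = 0.111.

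**Step 4: power in those cases.** In the worst cell (*e* = 15%, 100% vs 0%) the control mean is 1284 × 0.85 = 1091.4 and the CorPath mean is 1284 × 0.80 = 1027.2. The remaining difference is 64.2 mGy and power is about 93%. The next smallest difference is 1155.6 − 1027.2 = 128.4 mGy (*e* = 10%, 100% vs 0%). Power there and in all other cells is above 99%.

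**Step 5: no device effect, *e* = 5%.** Difference against the robot = 1284 × 0.05 × (*uC* − *uR*).

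| Uptake, control vs CorPath | Difference (mGy) | Chance of a significant result against the robot |
|---|---|---|
| 100% vs 0% | 64.2 | 93% |
| 100% vs 50% | 32.1 | 40% |
| 100% vs 75% | 16.1 | 13% |
| 100% vs 100% | 0 | 2.5% (nominal) |

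**The case against.** The asymmetry is a matter of silence. Section 7.2.5 gives recommended device steps and data milestones; it is not a full account of technique, and a line missing there does not tell operators to drop ordinary dose limitation. Both technique sections defer to outside sources, the Operator's Manual and the institutional procedure, and either may contain this advice. The steps are only encouraged, and nothing discourages them with CorPath. All PCIs take place at one hospital, and CorPath cases begin with conventional access and manual guide engagement, so habits are likely to carry over. These points stand. They make the 100% vs 0% rows a bound, not an expectation.

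The link to the sizing measure is also assumed. Collimation acts first on field area and so on DAP, whereas the sizing figures are in mGy. The percentages depend on the stated SDs as well. If both SDs were half of 1284 mGy (an assumption), the SE would be 642 × √(2/150) ≈ 74 mGy, and the 93% against the robot in Step 5 would fall to about 14%. Power for the same 64.2 mGy difference in Step 4 would fall equally. The figures are illustrations.

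Finally, the direction is conservative for a claim of robotic benefit, and encouraging good practice in the comparator avoids a weak control. That supports keeping the advice. It does not support giving it to one arm only. Because the sentence names the patient as well as staff, the operator's shielded cockpit does not explain the asymmetry either.

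**Conclusion.** The concern holds as a risk of performance bias. The Protocol gives dose-limiting advice to one arm of an open-label dose comparison, on the only outcome used to justify the sample size. Whether practice will differ is unknown, and so is the size of any bias. Under the assumed values, the observed reduction ranges from 5.9% in the extreme case to the full 20% at equal uptake. With a true 20% effect the test usually still succeeds on the stated SDs, so the harm falls mainly on the estimate. With no device effect there is a raised chance of a spurious finding against the robot. The point should be corrected. Confidence is medium, because the Operator's Manual and the institutional procedure are not available and uptake is not documented.

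**What to change.** Move the sentence on X-ray limitation, unchanged, from section 7.2.4 to a common procedure paragraph under section 7.2 that applies to both arms. Do not delete it, since it is radiation-safety advice. The clinical team should first confirm that it is compatible with the CorPath Operator's Manual.

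No new data item is needed. The listed data items do not record the steps themselves, but DAP and air kerma are already collected. Their ratio can be described by arm as a partial check on field size; it says nothing about table height.

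The cost is one moved sentence and one check against the manual. No extra data or staff are needed, and the sample size and stated power are unchanged.

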### CorPath Use Technique

The operator should refer to the CorPath GRX System Operator’s Manual for a detailed description of the system and relevant techniques.

To obtain proper data for analysis, the following procedure, with associated data collection milestones, is recommended, but in no case, dictates use of the CorPath GRX System in a manner different from that presented in the Operator’s Manual:

1. Obtain access using conventional percutaneous catheterization techniques.
2. Once arterial access is obtained, insert a standard guide catheter using conventional techniques. The guide catheter and guidewire of the physician’s choosing shall be used.
3. Manually advance and engage the guide catheter in the coronary artery. Perform angiography to assess the target lesion(s). Record target lesion characteristics such as percent diameter stenosis, etc.
4. Introduce and advance coronary guidewire utilizing CorPath GRX System to target lesion.
5. Record visual estimate of lesion segment (prior to pre-dilatation).
6. Introduce and advance the therapeutic coronary device (balloon/stent) using the CorPath GRX System. The delivery of interventional dilatation and stenting devices to the target lesion (pre-dilation, stent, post dilatation) will be done using the CorPath GRX System. Active guide management may be used to fine tune the placement of or reengage the guide catheter in the ostium of the coronary artery.
7. Measure target lesion using the CorPath GRX System as described in Section 3.5.
8. After stent placement, measure stent length using the CorPath GRX System as described in Section 3.5.
9. Retract balloon/stent system using CorPath GRX System.
10. Retract the guidewire using the CorPath GRX System.
11. Perform completion angiography to assess the target lesion final diameter stenosis and the condition of associated vasculature.
12. Record final fluoroscopy time.
13. Record time of guide catheter removal from the coronary vessel (procedure end time).

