### 1.3.1 Potential Risks

Participants may be exposed to potential risks from participating in this study. Potential procedure and device related adverse events that may occur and/or require intervention are described below. The primary risks of the procedure are believed to be similar to the risks of participants undergoing procedures requiring PCI. Complications may occur at any time during the procedure. Potential risks of the PCI are:

- Injury to the hearts arteries including tearing and rupture
- Infection, bleeding and bruising at the catheter site
- Allergic reaction or kidney damage due to the dye or contrast used
- Blood clots that can lead to stroke or heart attack
- Bleeding into the abdomen

This study involves exposure to a small amount of radiation during the coronary angiogram which the participant would be receiving as standard care. Radiation may slightly elevate the risk for cancer. There is no increase in risk of exposure as a result of participating in this study.

Complications may occur at any time during the procedure. The study may involve unknown or unforeseen side effects or complications other than those mentioned above.

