## **Other Measures/ Procedural Characteristics**

The objective of this study is to compare standard PCI with technology-assisted PCI to collect real-world data. When the PCI is being performed in conjunction with a diagnostic procedure, all efforts should be made to isolate the PCI procedural characteristics from the diagnostic procedure. At the end of the diagnostic procedure or alternatively to coincide with the PCI procedure time record the contrast, fluoroscopy time, DAP & AK at the end of the diagnostic procedure. When the PCI procedure is finished, record the values for these characteristics accumulated during the PCI procedure and not the diagnostic procedure. Procedures will be identified as staged (PCI only) or ad-hoc (LHC possible PCI). Any requirement to move from technology-assisted PCI to standard care will also be captured.

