### PCI Procedure Time

Defined as the time measured from the insertion of the guide catheter until removal of the guide catheter.

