### Equipment utilization (stents, wires, balloons, catheters)

### All equipment used in the PCI will be recorded to perform a cost analysis of technology-assisted PCI versus standard PCI performed by a cardiologist.

## **Lesion Assessment**

The lesion will be measured and recorded by the Cardiologist during the PCI. During the standard care PCI the Cardiologist will measure the lesion as per the institutional procedures. For the technology-assisted PCI the lesion length will be measured with the CorPath GRX System as per the Operations Manual.

The physician will attempt to use the same measuring technique for both pre and post lesion measurements (treatment length and stent length).

A comparison on lesion and PCI device length will be performed:

- 1. Length of segment needing intervention: visual estimate vs. CorPath GRX measurement.
  2. Length of stent(s): manufacturer’s labeled stent length(s) vs. CorPath GRX measurement of implanted stent length(s)

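### The implanted-stent measurement written only for the CorPath arm falls inside the dose and time windows and is not logged separately, so those comparisons may be biased against the robot by an unknown amount

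*Protocol*

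**What the plan says.** Protocol 7.2.5 gives a recommended sequence for CorPath cases, introduced as a way to obtain suitable data for analysis. Step 8 is: "After stent placement, measure stent length using the CorPath GRX System as described in Section 3.5". Retraction of the balloon or stent system and of the wire (steps 9 and 10), the final fluoroscopy reading (step 12) and guide catheter removal (step 13) all come later.

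Section 2.7 gives the use of the measurement: the manufacturer's labelled length is compared with the CorPath reading of the implanted stent. Section 7.2.4, on standard PCI, refers to the institutional procedure and lists no measurement of an implanted stent.

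PCI time is "Defined as the time measured from the insertion of the guide catheter until removal of the guide catheter" (2.6.2). Overall procedure time ends at the same point (2.6.1). Fluoroscopy time and DAP/air kerma are totals over the PCI (2.6.4, 2.6.5). The one separation rule, in 2.6, concerns diagnostic work: staff are to "record the values for these characteristics accumulated during the PCI procedure and not the diagnostic procedure".

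Section 8.1 sizes the trial on patient radiation alone: 150 per arm is "sufficient to detect a 20% reduction in radiation exposure to the patient during PCI". Section 1.3.1 tells participants: "There is no increase in risk of exposure as a result of participating in this study".

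**The concern.** The labelled length of an implanted stent is already known, so on the stated purpose step 8 serves a study comparison and not the choice of stent. It is nevertheless counted as part of the robotic PCI, and the text for standard PCI has no stated counterpart. A burden created by the trial in one arm could then be read as a property of the device.

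The outcomes exposed are overall time, PCI time and, if imaging is used, fluoroscopy time and patient dose. Patient dose is the only outcome in the sample size statement. The workload survey (2.8) covers the same procedure. A real dose reduction would look smaller than it is. With little or no true difference, the robot could look worse. Without readings taken around the step, the increment cannot be recovered after the case.

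**Working it through.** **Position of the step.** Set against the definitions in 2.6.1, 2.6.2, 2.6.4 and 2.6.5, step 8 comes after guide catheter insertion and before both the final fluoroscopy reading and guide catheter removal. It is inside all four windows. The rule in 2.6 removes diagnostic values only. For the two time outcomes no further assumption is needed: whatever time step 8 takes is counted in the CorPath arm. For dose and fluoroscopy an assumption is needed, because no section says that the measurement uses X-ray or how long it lasts. The technique is referred to Section 3.5, but Section 3 ends at 3.4.

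**The plan's own figure (8.1).** Inputs: control mean 1284 mGy, SD 180; CorPath SD 142.83; 150 per arm; 20% reduction; two-sided 5%.
- Planned difference: 0.20 × 1284 = 256.8 mGy, so the CorPath mean is 1027.2 mGy.
- SE = √(180²/150 + 142.83²/150) = 18.76 mGy.
- Difference/SE = 256.8/18.76 = 13.7, so power is about 1.000. The stated power above 99% is reproduced.

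**Effect of an added dose, with a true 20% reduction.** The protocol gives no figure for step 8, so the fraction f of the CorPath mean is an assumption. Apparent difference = 256.8 − f × 1027.2; apparent reduction = that difference/1284.

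| f (assumed) | Added dose, mGy | Apparent difference, mGy | Apparent reduction | Power |
|---|---|---|---|---|
| 2% | 20.5 | 236.3 | 18.4% | >99.9% |
| 5% | 51.4 | 205.4 | 16.0% | >99.9% |
| 10% | 102.7 | 154.1 | 12.0% | >99.9% |
| 15% | 154.1 | 102.7 | 8.0% | 99.98% |
| 20% | 205.4 | 51.4 | 4.0% | 78% |
| 25% | 256.8 | 0 | 0% | none |

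Power stays at or above 80% until about 204 mGy is added.

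**Effect of an added dose, with no true difference.** Here both means are 1284 mGy. An addition equal to 1.96 × 18.76 = 36.8 mGy (36.8/1284 = 2.9%) would by itself reach the significance limit. The chance of a significant excess for CorPath is about 28% if step 8 adds 2% (25.7 mGy) and about 93% if it adds 5% (64.2 mGy). If the SD were 60% of the mean, also an assumption, the 5% case falls to about 11%.

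**Larger SDs with a true 20% reduction (assumption).** At three times the plan's SDs, power falls from 99.5% to 95.4% (5% added) or 78.2% (10% added). At five times, it falls from 78.2% to 59.1% or 37.5%.

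**The case against.** A reader might infer that the radiation comparison is biased, that step 8 is purely a research act, and that standard PCI has nothing like it. The documents do not support any of these as fact.

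- No section says that the measurement uses X-ray, so for the sized outcome even the existence of a bias is conditional.
- The steps are recommended and defer to an Operator's Manual that is not at hand. The protocol never says that measurement after stenting lies outside ordinary device use, and 1.2 presents better measurement accuracy as a clinical improvement of the device.
- Section 2.7 has a sentence on measurements before and after treatment, including stent length, that names no arm. Section 7.2.3 lists the operator's assessment of stent length and the number of uses of stent visualisation, also without an arm. Standard operators may image the implanted stent inside the same window.
- The 2% to 25% additions have no source in the protocol. The 93% figure needs a 5% addition, no true difference and the plan's SDs all at once.
- Subtracting step 8 from the CorPath arm alone could favour the robot if it replaces imaging that manual operators keep in their totals.

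All of this stands, and it limits the point to a possible bias of unknown size. It does not remove the structural fact: the step is written for one arm, for a listed study comparison, inside every window and without separation. Because the steps are only recommended, they may be performed unevenly, which makes a record of them more useful.

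**Conclusion.** The point holds in conditional form. Any time spent on step 8 counts against CorPath in both procedure times. If the step uses X-ray, it also adds fluoroscopy and dose to that arm. The amount is unknown.

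On the plan's SDs the planned test is robust: a true 20% reduction stays detectable with power above 99% at assumed additions up to 15%. What is exposed is the size of the estimate, or a false signal for CorPath if the true difference is small. An established bias, or an under-powered trial, should not be read into this.

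The conflict with the exposure sentence in 1.3.1 is likewise conditional: it arises only if step 8 uses X-ray. The change is still worth making, because it is cheap, it protects the outcome on which the trial is sized, and the increment cannot be reconstructed later.

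**What to change.** - **7.2.5:** record clock time, fluoroscopy time, DAP, air kerma and contrast volume immediately before and after step 8, as 2.6 already requires at the end of the diagnostic part.
- **8.1:** keep the full-window comparison as it is. Add a pre-specified sensitivity analysis of dose, fluoroscopy time and both procedure times that excludes the step 8 segment.
- **2.7:** state which arms measure the implanted stent. If standard PCI does so too, log it in the same way.
- **7.2.5:** correct the reference to Section 3.5 in steps 7 and 8.
- **1.3.1:** if step 8 uses X-ray, reconcile the exposure sentence with it.

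Cost: two sets of readings for each step 8 measurement (five quantities, so about ten values, and more where a participant has several stented lesions), the matching eCRF fields and one added analysis. No extra participants are needed. The workload score cannot be corrected this way, because the survey is completed once, after the procedure; that limit should be stated when the survey is reported.

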### Overall Procedure Time Measure

Defined as the time measured from the insertion of the hemostasis sheath until the removal of the guide catheter

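### Step 13 of the CorPath technique stops the procedure clock at a different event from the outcome definitions; followed literally, it may shorten both procedure times in robotic cases

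*Protocol*

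**What the plan says.** Four places in the protocol bear on when the procedure clock stops.

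- Section 2.6.1, overall procedure time: "Defined as the time measured from the insertion of the hemostasis sheath until the removal of the guide catheter".
- Section 2.6.2, PCI procedure time: "Defined as the time measured from the insertion of the guide catheter until removal of the guide catheter". The summary table at the front gives the same end event for both measures.
- Section 7.2.3, the list of data collected during the procedure: "Procedure end time (Guide Catheter out". This list is not split by arm.
- Section 7.2.5, CorPath Use Technique, step 13: "Record time of guide catheter removal from the coronary vessel (procedure end time".

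The CorPath step list is introduced with "To obtain proper data for analysis, the following procedure, with associated data collection milestones, is recommended". The matching section for the control arm (7.2.4) says "PCI will be performed as per the Institutional PCI procedure" and contains no timing milestone.

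Under Statistical Methods (8.1), procedure times fall under the rule for remaining outcomes: "continuous outcomes will be measured using independent t-test (or non-parametric alternative depending on distributional assumptions".

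**The concern.** The label for procedure end time is attached to two events. In 7.2.3 it means the guide catheter is out. In step 13 it means the guide catheter has left the coronary vessel. Both procedure times share this end point, so any discrepancy enters both outcomes by the same number of minutes.

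The step 13 wording stands only in the robotic technique section. An end event that came earlier in one arm would be a measurement difference tied to treatment, and randomisation does not remove that. It would overstate any time saved by the robot, or understate any extra time it needs. If only one time stamp is recorded per case, nobody could later tell which event it refers to.

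**Working it through.** **1. Are these different events in the protocol's own terms?** Three places suggest that they are.

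- Steps 2 and 3 of 7.2.5 treat inserting the guide catheter and engaging it in the coronary artery as separate actions.
- The Background (1.2) describes the guide catheter losing its seat in the coronary ostium during a case and being re-engaged. Leaving the coronary is therefore not the same as being removed.
- Section 7.2.2 starts the PCI clock at guide catheter insertion, not at engagement. Under 2.6.2 the clock runs from insertion to removal. Under step 13 read literally, it would run from insertion to disengagement.

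**2. Which text applies to which arm?**

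| Source | Arm covered | End event |
|---|---|---|
| 2.6.1, 2.6.2, summary table | both | guide catheter removal |
| 7.2.3 data list | both (it includes robot-specific items) | guide catheter out |
| 7.2.5 step 13 | robotic only; recommended | removal from the coronary vessel |
| 7.2.4 | standard only | none of its own; general definition applies |

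A standard case has one rule. A robotic case has two, and the step list presents itself as the route to proper analysis data. Any shift from following step 13 literally therefore shortens robotic times only.

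**3. Size.** The protocol gives no SD for procedure time and no interval between the two events. Its only computed figure concerns radiation: "A total sample of 300 patients (150 in each group) is sufficient to detect a 20% reduction in radiation exposure", with power above 99%. That figure reproduces. The difference is 0.20 × 1284 = 256.8 mGy. The combined SD is √((180² + 142.83²)/2) = 162.48 mGy. Power at 150 per arm is about 1.00, and about 15 per arm would give 99%. The figure says nothing about procedure time.

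What follows is an illustration under assumed values only. Let b be the mean shortening in the robotic arm in minutes, let true times be equal, and assume 150 analysed per arm.

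- Standard error of the difference: SE = SD × √(2/150) = SD × 0.1155
- Two-sided rejection probability: 1 − Φ(1.96 − b/SE) + Φ(−1.96 − b/SE)

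Example with SD 20 and b = 1: SE = 2.31, b/SE = 0.43, rejection probability 7.2%.

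| Assumed SD (min) | SE (min) | b = 0.5 | b = 1 | b = 2 | b = 3 |
|---|---|---|---|---|---|
| 10 | 1.15 | 7.2% | 13.9% | 41% | 74% |
| 15 | 1.73 | 6.0% | 8.9% | 21.1% | 41.0% |
| 20 | 2.31 | 5.5% | 7.2% | 13.9% | 25.5% |
| 30 | 3.46 | 5.2% | 6.0% | 8.9% | 13.9% |

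Here b is an average over the whole robotic arm. If a fraction f of robotic cases follows step 13 and the gap is g minutes, then b = f × g. Half the cases with a 2-minute gap gives b = 1. The right-hand columns need a long gap in every robotic case and in no control case.

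**The case against.** The strongest reply is that the protocol already fixes the end event. The outcome definitions apply to both arms. The list in 7.2.3 plainly covers robotic cases, since it includes a robotic stent-length assessment and the use of robotic algorithms. The step list is a recommendation. This is a single-centre trial, and 9.1 plans training meant to make data collection uniform. Step 13 is also the last step, with no later withdrawal listed, so it may be a loose description of ordinary removal. None of the other passages says what the catheter is to be out of.

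Much of this stands. A reader might infer that robotic times are cut short in this trial. The documents do not support that: it would take staff preferring step 13's literal wording to the outcome definitions and the common data item. A reader might also infer that the uncounted interval contains the time spent releasing the catheter from the cassette. Section 5.1.3 says only that the cassette holds the guide catheter hub. Nothing states when the hub is released relative to disengagement, so that mechanism is not established.

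The reply does not remove the conflict. The loose-wording reading is possible, but it is not the natural one in a protocol that elsewhere separates engagement from insertion and disengagement from removal. That the list is only recommended means some robotic cases could be timed one way and some the other. Training cannot settle the matter while the text being trained on says both.

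**Conclusion.** The inconsistency is real and can be seen from the text alone. Step 13 gives the procedure end time an event that, read literally, precedes the one in 2.6.1, 2.6.2, 7.2.3 and the summary table, and it does so for the robotic arm only. The consequence is conditional: overall and PCI procedure time may be measured differently by arm, in the robot's favour, if step 13 is followed as written.

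The size cannot be derived from the protocol. It is small if withdrawal is quick: for an assumed mean shift of 0.5 to 1 minute and an SD of 15 to 30 minutes, the false-positive rate is 5.2% to 8.9% instead of 5%. Higher rates in the table are illustrations under less favourable assumptions, not estimates for this trial. They use a normal approximation to the t-test, and the protocol also allows a non-parametric test.

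The importance is limited. Procedure times are listed among other measures, and the trial was sized on patient radiation exposure. The end-time label does not affect radiation dose, fluoroscopy time, clinical success or MACE. This is a minor wording correction to two comparative outcomes.

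**What to change.** Reword step 13 of 7.2.5 to match 2.6.1, 2.6.2 and 7.2.3: drop the reference to the coronary vessel and tie the step to the catheter-out event, for example *Record time of guide catheter removal (Guide Catheter out; procedure end time)*. Add one sentence, in 2.6 or 7.2.3, saying that the same end event is recorded in robotic and standard cases. Use the same wording as the label of the eCRF field.

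No new end point, such as exit from the sheath, is needed; the existing definitions suffice once step 13 agrees with them. The cost is one line of protocol text, one added sentence and a check of a field label. It adds no work during the procedure and does not change how the procedure is done.
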